### Plans to give access to the full protocol, participant-level data, and statistical code {31c}

The pseudonymized dataset and syntaxes can be made available by the corresponding author upon reasonable request and in accordance with the transfer guidelines of Leiden University.

### Composition of the data monitoring committee, its role and reporting structure {21a}

Monitoring of the conduct of the study will be performed by an independent data manager who is not involved in the study. The data manager will check whether the data that have been entered in the database match the source data by random sampling and guarantee the anonymity of the personal data. As per the protocol that has been set up for data management in the Health, Medical and Neuropsychology unit of Leiden University, the data manager will be responsible for checking the data during the recruitment period as well as the final check of the data at the end of the study.

### Adverse event reporting and harms {22}

All adverse events (AEs) reported spontaneously by the participant or observed by the investigator or staff will be recorded. Serious adverse events (SAEs) will be reported by the study staff to the accredited METC that approved the protocol, within 7 days of first knowledge for SAEs that result in death or are life threatening followed by a period of maximum 8 days to complete the initial preliminary report. All other SAEs will be reported within a period of maximum 15 days after the sponsor has first knowledge of the serious adverse events. Reporting suspected unexpected serious adverse reactions (SUSARs) is not applicable, since this study does not include a medicinal product.

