Despite the benefits of CBT for patients with a chronic condition, some patients experience barriers that prevent them from participating in psychological interventions, such as time constraints, a lack of availability of services, financial problems, problems in transportation to care [32], and the remaining stigma on mental illness [33, 34]. A solution to overcome these barriers is to offer CBT online. In Internet-based CBT (ICBT), patients have the freedom to select the time and place that best suits their schedule, while following treatment at home lowers the threshold of seeking psychological support [35, 36]. Especially for dialysis patients—considering their numerous visits to the clinic, mobility problems, and high disease burden—this would make CBT more accessible, convenient, and less burdensome. In addition, for therapists, offering CBT online is time-efficient and enhances flexibility which, in turn, results in reduced costs and shorter waiting lists [36].

ICBT interventions usually consist of guided self-help formats in which patients are supported by a therapist through short messages, telephone, or videoconference [37]. ICBT is found to be as effective as face-to-face CBT in improving both mental (e.g., anxiety and depression) [38, 39] and physical functioning (e.g., disease-specific quality of life, irritable bowel syndrome symptoms, headache, pain severity, disability, and fatigue) [37–39] in several somatic conditions. Compared to self-guided interventions, interventions guided by a therapist are found to result in better outcomes [40, 41]: therapist support does not only increase adherence and prevents drop-out [35], it also allows for therapists to tailor the intervention to individual patient needs, which increases the effectiveness of (I)CBT [19, 35].

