**Secondary outcomes**						
Personalized outcome assessment	Patient Priority and Progress Questionnaire (PPPQ) [46]	Patient priorities and personal meaningful changes over time. Measured by 1 item on priorities and 8 items on functioning using 5-point Likert scales for the baseline measurement and 7-point Likert scales for the follow-up measurement. Based on the follow-up measurement, a progress score is calculated on the selected priority.	−3–3, progress score, higher scores indicate subjective improvement on the selected priority as compared to the baseline measurement.	X	X	X
Domains of functioning	RAND Short Form-36 Health Status Inventory (RAND SF-36) [47]	Health-related quality of life, including physical and mental component scores. Measured by 36 items using several Likert scales and yes/no questions.	*T*-scores, *M*=50±10 in the general population.	X	X	X
	Dialysis Symptom Index (DSI) [48]	Physical and emotional symptom burden in dialysis patients. 30 items regarding the presence of symptoms, when present symptom severity is assessed by 5-point Likert scales.	30 yes/no questions, if “yes” 1=not at all, 5=very much. Minimum score is 0 when none of the symptoms are reported. Maximum score is 150 when all 30 symptoms are reported and rated as “bothers very much” (Likert scale score 5).	X	X	X
	Subjective experience of fatigue subscale, Checklist Individual Strength (CIS) [49]	Fatigue. Measured by 8 items using 7-point Likert scales.	8–56, higher scores indicate more fatigue.	X	X	X
	Itch subscale of the Impact of Chronic Skin Disease on Daily Life (ISDL) [50]	Itch. Measured by 4 items including 3 items using 4-point Likert scales and 1 VAS (0 = no itch, 10 = worst itch ever).	4–16, the 11-point VAS will be transformed into a 4-point Likert scale to assess the total score. Higher scores indicate more itch.	X	X	X
	Inventory for Social Resilience (ISR) [51]	Social functioning. Measured by the subscales perceived support (5 items), actual support (3 items), and mutual visits (2 items) using 4-point Likert scales.	5–20, perceived support. 2–13, actual support. 2–8, mutual visits. Higher scores indicate better social functioning.	X	X	X

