### Intervention description {11a}

#### Procedure E-HELD intervention

Participants allocated to the intervention condition will receive tailored ICBT. The ICBT intervention is guided by a trained psychologist, referred to as the “e-Coach.” All e-Coaches participating in this study have a master’s degree in health or clinical psychology and are supervised by a senior clinical psychologist with post-academic training in CBT. Treatment starts with a face-to-face intake meeting with the e-Coach. When a face-to-face meeting is not possible, the e-Coach will schedule a digital, videoconferencing meeting instead. During the intake, the patient will receive feedback on the screening results using the Personal Profile Chart in which the results are visualized. Based on the discussion of patient’s results, the patient and the e-Coach will determine patient’s top priorities for improvement and formulate treatment goals. Subsequently, the e-Coach will tailor the intervention so that it meets the patient’s needs. In addition, the e-Coach will explain the online environment and explores the patient’s wishes with regard to the intensity and the form of the treatment (e.g., the amount of exercises, a wish for additional phone calls, or a preference for reading texts or practical exercises). Subsequently, the patient will work on the homework assignments for 3 to 4 months.

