#### Characteristics E-HELD intervention

The E-HELD intervention includes modules on coping with fatigue, itch, pain, physical disabilities, negative mood, social relations, and lifestyle. In consultation between patient and e-Coach, one or two modules will be chosen based on the screening results and patient’s priorities. Consequently, every patient’s treatment has a unique character, especially since within each module different exercises can be chosen. Exercises include several homework assignments such as reading psychoeducational texts and completing personal assignments (e.g., keeping a diary of daily activities) and exercises (e.g., relaxation). Using a message box in the online environment, the e-Coach will provide weekly personalized feedback on the exercises and send motivational messages. The patient can respond to the e-Coach’s messages or ask questions via the same message box. After 3 to 4 months, the e-Coach will contact the patient for an end-of-treatment consultation to end treatment with a final module on setting long-term goals and preventing relapse.

All modules consist of evidence-based cognitive-behavioral techniques that target risk and resilience factors and were developed from standardized CBT protocols of patients with various chronic somatic conditions [68–70]. Studies on psoriasis and rheumatoid arthritis using this intervention showed promising effects on improved physical functioning and a reduced impact of disease on daily life [70, 71]. For the current study, we tailored the intervention to the needs of dialysis patients based on the results of a previous study on patient priorities [15]. Additionally, we adjusted the itch module making it suitable for dialysis patients and added lifestyle modules to support patients in adherence to medication, physical exercise, diet restrictions, and to quit smoking. For more information on the development of the intervention for the CKD and dialysis population, please see the development and treatment protocol [67].

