### Criteria for discontinuing or modifying allocated interventions {11b}

When a patient’s health significantly worsens over the course of the study, the e-Coach will discuss together with the patient to either discontinue treatment, set the treatment on hold with the possibility to continue in the future, or continue treatment in an adjusted manner (e.g., lower the amount of assignments).

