#### Personalized outcome assessment

The Personalized Priority and Progress Questionnaire (PPPQ) [46] is a personalized instrument to identify, prioritize, and monitor individual problems over time. The baseline measurement consists of 8 items on several domains of functioning that have proven relevant for dialysis patients in a previous study in the Netherlands, including physical health (e.g., fatigue, pain, itch), mental health (e.g., anxiety, depression), social functioning (e.g., dependence on others), and daily activities (e.g., work, hobbies) [15]. In addition, the PPPQ includes 1 item on priorities: patients are asked to select the domains they prioritize for improvement by making a top 3. The follow-up measurement assesses the amount of progress in the areas of functioning over the past 6 months (8 items). Additionally, patients indicate on which of these areas they actively worked in the previous months (1 item). Higher scores on the follow-up measurement indicate improved functioning.

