### Plans to promote participant retention and complete follow-up {18b}

The assessments consist of online questionnaires that participants can complete at home, at a moment that suits them. To split up completion time, participants can pause the questionnaires at any moment and continue completion within the next 14 days. To promote participant retention in the intervention condition, we will tailor the treatment to the participant’s wishes, needs, and abilities. In addition, the e-Coaches will regularly ask patients for feedback to make adjustments if necessary. This could mean, for example, that for a given patient treatment will include less psychoeducational texts, more practical exercises, and additional phone calls with the e-Coach therapist.

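### Adverse events are captured passively and only the ICBT arm has e-Coach contact, so an adverse-event table by arm would probably over-record non-serious and psychological events under ICBT

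*Protocol article*

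**What the plan says.** Under Adverse event reporting and harms {22}, the protocol article states: "All adverse events (AEs) reported spontaneously by the participant or observed by the investigator or staff will be recorded". The rest of that section gives timelines for reporting SAEs to the ethics committee. No scheduled adverse-event question is described for either arm.

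Contact with the study team differs by arm. For ICBT, "Treatment starts with a face-to-face intake meeting with the e-Coach" (Procedure E-HELD intervention). After that, "the e-Coach will provide weekly personalized feedback on the exercises and send motivational messages" (Characteristics E-HELD intervention). The same section gives patients a message box for replies and an end-of-treatment consultation. If health worsens significantly, "the e-Coach will discuss together with the patient to either discontinue treatment, set the treatment on hold", or continue it in adjusted form (section {11b}). Controls receive care as usual.

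Much contact is shared. The Background describes dialysis patients by "considering their numerous visits to the clinic, mobility problems, and high disease burden". Section {6b} describes usual care as multidisciplinary, guided by complaints and patient-reported measures, with specialized social workers, and with a psychologist or psychiatrist available when needed.

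**The concern.** When events are recorded only if volunteered or noticed, the count depends on how often someone is there to hear or notice. ICBT patients have one more listener than controls, a psychologist with whom they discuss matters such as pain, fatigue, itch or low mood. Non-serious events and psychological worsening are the ones most likely to be mentioned there and nowhere else.

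The stake is how an adverse-event table by arm in the trial report would be read. An excess under ICBT could not be separated from better ascertainment. The affected events are also those most relevant to a psychological intervention.

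**Working it through.** The article states no adverse-event rate, so there is no figure to reproduce. The check compares the routes by which an event can be recorded, and then asks what can be quantified.

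**Routes by arm**

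| Route | ICBT | Control |
|---|---|---|
| Dialysis team, nephrologist, social worker ({6a}, {6b}) | yes | yes |
| Online questionnaires at baseline, 6 and 12 months ({18a}) | yes, not named as an adverse-event source | same |
| e-Coach intake, weekly messages, reply box, closing consultation | yes, over 3–4 months | none |
| Log of content, frequency and duration of e-Coach contact (Table 1) | yes | none |

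**Extent of the extra route** (treatment length from the intervention sections, follow-up from {18a})
- Share of the 12 months: 3/12 = 25% to 4/12 = 33%.
- Share of the first 6 months: 3/6 = 50% to 4/6 = 67%.
- Weekly e-Coach messages: 3 × 52/12 = 13.0 to 4 × 52/12 = 17.3, plus 2 consultations.

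These count opportunities for contact. They do not count reported events.

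**Weight of one patient** (65 per arm, Sample size {14}): 1/65 = 1.54 percentage points on the ICBT rate for each patient whose event is known only through the e-Coach.

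**Direction, with assumed inputs.** Let p be the true risk, equal in both arms. Let c be the probability of capture by shared routes, and e the probability that the e-Coach route captures an event the shared routes would miss. None of the three is in the article.
- Recorded risk, control: p × c.
- Recorded risk, ICBT: p × [1 − (1 − c)(1 − e)].
- Ratio: [1 − (1 − c)(1 − e)]/c, which does not depend on p.

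| c | e | Ratio | Expected recorded patients, control vs ICBT (p = 0.30, n = 65) |
|---|---|---|---|
| 0.7 | 0.1 | 0.73/0.7 = 1.04 | 13.7 vs 14.2 |
| 0.5 | 0.1 | 0.55/0.5 = 1.10 | 9.8 vs 10.7 |
| 0.5 | 0.2 | 0.60/0.5 = 1.20 | 9.8 vs 11.7 |
| 0.5 | 0.4 | 0.70/0.5 = 1.40 | 9.8 vs 13.7 |
| 0.3 | 0.4 | 0.58/0.3 = 1.93 | 5.9 vs 11.3 |

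The ratio exceeds 1 whenever e > 0 and c < 1. It tends to 1 as c approaches 1, which is the expected case for deaths and hospital admissions. It equals 1 when e = 0, either because e-Coach information never enters the event record or because the comparison uses only sources common to both arms. The range 1.04 to 1.93 reflects the assumed inputs and is not an estimate for this trial.

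**The case against.** The strongest reply is that no planned analysis is touched. The objectives, outcomes and statistical methods contain no comparison of harms by arm. This stands: the point concerns a table that the report may contain, and efficacy is unaffected.

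The e-Coach route can also be overread. No section says that e-Coaches record adverse events. That they are staff is an inference, though a reasonable one, since the article describes them as psychologists taking part in the study. A reader might also infer from "the e-Coaches will regularly ask patients for feedback to make adjustments if necessary" (section {18b}) that e-Coaches routinely ask about health problems. The sentence that follows gives fewer texts, more practical exercises and extra phone calls as examples, so the feedback concerns the format of treatment. Section {11b} says what the e-Coach does once health has worsened, and does not say that the e-Coach detects or logs it.

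Shared surveillance also covers psychosocial problems: usual care in both arms uses patient-reported measures and social workers for them. This reduces the gap but does not close it.

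A reader might further infer that a true reduction in deterioration under ICBT would be hidden. The document does not support that. The PHQ-ADS is collected in both arms at 6 and 12 months, so psychological deterioration can be compared symmetrically on the primary scale. The problem is confined to the adverse-event record.

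Finally, elicitation details could sit in the full protocol. The capture method itself, however, is stated in the article, and it is the stated method that is unequal between arms.

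**Conclusion.** The point holds in a limited form. Passive recording combined with e-Coach contact in one arm gives unequal ascertainment of non-serious and psychological events. If e-Coaches count as staff, a table by arm would probably over-record these under ICBT. The amount cannot be derived from the article, and frequent shared dialysis-care contact makes it smaller. Deaths and hospitalizations should be little affected, and the efficacy analysis is not affected at all.

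The conclusion rests on two assumptions: that what e-Coaches learn reaches the event record, and that shared routes do not already capture every such event. It does not show that the trial would misstate safety overall. The likely direction is against ICBT. It is worth correcting because most of the data for a symmetric comparison are already collected.

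**What to change.** Keep section {22} for event recording and SAE reporting, and add:

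1. A source field on the event form (e-Coach, centre staff, participant, questionnaire), with e-Coach-only events reported separately.
2. Any comparison of harms by arm based on sources identical in both arms:
   - PHQ-9 ≥20 or GAD-7 ≥15 at 6 or 12 months. These are the red cut-offs in Table 2, and patients at or above them at screening are excluded, so any later occurrence is new.
   - Hospitalizations from the iMCQ.
   - For participants still to be assessed, one fixed adverse-event question in the 6- and 12-month questionnaires.

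Leave the PPPQ out, or use only the progress score on the selected priority. Table 1 gives its −3 to 3 range for that score, not for each of the eight items. The reference period is also unclear. Section Personalized outcome assessment says "The follow-up measurement assesses the amount of progress in the areas of functioning over the past 6 months (8 items", whereas Table 1 says "higher scores indicate subjective improvement on the selected priority as compared to the baseline measurement". At 12 months these differ.

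**Cost.** One field on the event form and one question at two time points. The other measures are already collected in both arms. The new question needs an amendment approved by the ethics committee. Recruitment began in February 2019, so participants already past an assessment will not have answered it there.

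**Limits.** Events can be forgotten over the recall period, and the article does not state the iMCQ recall period. All these sources are self-reports by unblinded patients, so the opportunity to report is equalized but expectations are not. Questionnaire non-responders are lost, and the Discussion expects drop-out from poor computer skills and high disease burden. The number assessed per arm should therefore accompany each harms figure.

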### Frequency and plans for auditing trial conduct {23}

The study staff will submit a summary of the progress of the trial to the accredited METC once a year. Information will be provided on the date of inclusion of the first subject, numbers of subjects included, and numbers of subjects that have completed the trial, serious adverse events/ serious adverse reactions, other problems, and amendments.

### Plans for communicating important protocol amendments to relevant parties (e.g., trial participants, ethical committees) {25}

All protocol amendments will be approved of by the METC prior to implementation. If relevant, participants will be informed of protocol modifications.

### Dissemination plans {31a}

Results will be reported in national and international conferences and submitted for publication in peer-reviewed journals.

## Discussion

ICBT is increasingly used in patients with chronic somatic conditions to treat psychological problems such as anxiety and depression and to support patients in adjustment to illness, treatment adherence, and self-management. Results from meta-analyses and systematic reviews suggest promising effects for both psychosocial and disease-specific outcomes of ICBT in several chronic somatic conditions, especially when guided and tailored to specific patient needs [37–39]. However, when it comes to the dialysis population, almost no adequately powered studies and no tailored studies are available.

The few studies that have focused on dialysis patients found improvements in anxiety, depression, and HRQOL, but found mixed results on the experienced burden of kidney disease on daily life and no effects on disability [42, 43]. In terms of the feasibility of the ICBT interventions, challenges were found with regard to computer literacy. Nonetheless, positive results were found with regard to the acceptability of the treatment [42, 44]. Since these results were derived from underpowered and/or non-controlled studies, more research is needed to evaluate the effectiveness of ICBT in dialysis patients.

The current study will assess the effectiveness of a guided ICBT intervention that is specifically developed for dialysis patients and that will be tailored to individual patients’ needs using a multicenter randomized controlled trial. To evaluate the effectiveness of the intervention, we will primarily look at distress, but furthermore take the personalized character of the treatment into account by examining effects by means of a personalized outcome instrument and several secondary HRQOL variables. In addition, the potential role of demographic, clinical, and psychological parameters in determining treatment outcome will be assessed, as well as the cost-effectiveness of the intervention. When the ICBT intervention proves to be effective, the intervention could be implemented in standard care and patients could be offered a personalized treatment supporting them in the problems they prioritize for improvement.

A unique feature of this study is the use of an innovative screening tool to detect patients with an increased risk for adjustment problems such as physical problems, limitations in daily life, and distress. The domains included in the screening tool were based on a previous study of our group in which we evaluated patients’ most prominent problems from a patient perspective [15], to ensure that the screening tool detects what matters most to patients. In addition, the screening tool includes validated screening questionnaires and makes use of disease-specific norm scores, allowing clinicians and patients to compare the individual patient’s scores to other dialysis patients. In previous research, dialysis patients have indicated that they feel reference scores would help to better understand the meaning of their results and indicated to find it highly valuable to receive feedback on their results [9]. To meet these needs, patients’ results will be visualized in a Personal Profile Chart. This chart presents feedback on patients’ results in a way that is easy to understand by using traffic light colors and text boxes with additional explanations [67]. By sending these to all patients who filled out the screening questionnaires, irrespective of whether or not they were eligible for the intervention, patients are provided with feedback on their functioning and are encouraged to discuss this Profile Chart with their nephrologist during a regular consultation.

Another strength of the intervention are the multiple options for tailoring. The ICBT intervention includes modules focusing on issues that patients have indicated to be a priority for improvement as found by a previous study [15], making this intervention a suitable and personally meaningful option for every dialysis patient. Additionally, the intervention will be guided by a therapist, as research showed that therapist-guided interventions yield better results and allows for tailoring of the intervention [19, 40, 75]. At the start of the intervention, the e-Coach uses the patient’s Personal Profile Chart to determine treatment goals together with the patient and, subsequently, tailors the intervention to the patient’s needs. During treatment, the e-Coach continues to tailor the intervention by monitoring whether the form and intensity of the intervention still matches the patient’s preferences and abilities and to make adjustments if necessary.

There are several limitations to consider. As found in previous studies on ICBT in dialysis patients, challenges with computer literacy are likely to occur. This could result in lower inclusion rates due to patients not having access to a computer or Internet. In addition, when patients are enrolled in the study, poor computer skills could lead to drop-out when participating in the study appears to be too difficult. To minimize the risk of drop-out, the therapists who guide the intervention will be highly attentive of these difficulties and will make adjustments if the intervention appears to be too difficult. For example, therapists could choose to communicate via telephone instead of online text messages. Another risk for drop-out is patients’ high disease burden. This risk could be minimized in the same way: regularly monitoring whether ICBT treatment matches the patient’s abilities and making adjustments if necessary (e.g., lowering the intensity).

In conclusion, the present study design will provide insight in the effectiveness of a patient-priorities tailored ICBT intervention in patients with kidney failure who are treated with dialysis. When tailored ICBT proves to be a valuable and effective intervention, the screening procedure and the subsequent ICBT intervention could be implemented in routine care to detect, support, and treat patients struggling with adjustment problems.

